### Ethics and dissemination

The study has received ethical review board approval (number 2015–004613-24). Data on the recruitment, efficacy, safety, protocol updates and all aspects concerning good clinical practice are reviewed by the data safety monitoring board, which consists of an internal medicine physician, a pharmacist and an epidemiologist.

## Discussion

In designing this research protocol, we needed to address a number of clinical and methodological issues. First, patients who are still in the inflammatory phase of the disease are more likely to respond to treatment with glucocorticoids; therefore, the choice was made to include only patients who fulfil the VEDOSS criteria, but not the 2013 ACR/EULAR classification criteria, for SSc [28].

Second, treatment consisting of short pulses of methylprednisolone is often better tolerated than continuous high oral doses, while fewer long-term consequences are seen when using short methylprednisolone pulses. The choice of an intravenous infusion of high-dose (1000 mg) methylprednisolone was based on the treatment regimens in other auto-immune diseases, such as lupus nephritis and dermatomyositis, in cases of exacerbation or failing standard therapy or both [9, 10]. In these diseases, high-dose methylprednisolone has been shown to induce remission. The schedule of three consecutive days of treatment during three consecutive months was chosen because this method is generally used in severe autoimmune diseases.

Disease activity in SSc is measured mostly by mRSS and, in cases with pulmonary involvement, by pulmonary function results. However, to date, no biomarkers are available to follow-up the disease activity. The use of vasculopathy and inflammatory biomarkers, as well as clinical signs and symptoms, as endpoints in our study, enables us to meet the patient need for alternative markers on disease activity, as the known signs and symptoms of worsening prognosis are present in only a minority of patients.

This trial is the first to aim to treat very early SSc and is promising because it targets the early stages in the disease process using a relatively safe and inexpensive treatment known to be highly effective against inflammation. If it is possible to prevent significant clinical disease in patients with very early SSc by using a safe treatment, this will cause a paradigm shift in scleroderma care and research. The knowledge gained from this project will facilitate further research into the efficacy and safety of using high-dose glucocorticoids in SSc treatment and enable this treatment to progress through a pivotal phase III trial. We anticipate that, if successful, this project will enormously increase research efforts into the early treatment of SSc and decrease the cost of health care for these patients.

In this trial, patients with SSc receive treatment very early in the progression of their disease, which could change the long-term outcome of SSc. In current daily practice, patients so early in the disease course do not receive treatment, although they can be at risk for early escalation and internal organ involvement, reducing their prognosis. A trial to investigate the efficacy of treatment using high-dose glucocorticoids will provide us with the opportunity to change this disease course, reducing the disease burden of a portion of patients with SSc. If the treatment of very early SSc with high-dose glucocorticoids is effective, this will prelude a pivotal change in the treatment of SSc.

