### Participants, intervention and outcomes

#### Inclusion criteria

Patients who meet the following criteria at randomisation are eligible for the study:age of more than 18 years,fulfil VEDOSS criteria [16]: Raynaud’s phenomenon AND positive test for anti-centromere or anti-topoisomerase antibodies AND nailfold capillaroscopic findings typical of SSc,puffy fingers for less than 3 years, andmRSS of 0.

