#### Exclusion criteria

Patients who, at randomisation, meet any of the following criteria are not eligible for the study:presence of acrosclerosis, acro-osteolysis or digital ulcers,presence of anti-RNA polymerase III auto-antibodies,previous systemic treatment for SSc, namely methotrexate, prednisone (>14 days in the previous 6 months), mycophenolate mofetyl or cyclophosphamide,clinically significant internal organ involvement: diffusing capacity for carbon monoxide (DLCO) less than 80% predicted, vital capacity less than 70% predicted, renal dysfunction with glomerular filtration rate less than 60 mL/min, diastolic dysfunction more than grade 1 on echocardiography, pulmonary hypertension, or weight loss more than 10% in the last 6 months with unknown cause, andcontra-indications for methylprednisolone.

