#### Secondary outcomes

The secondary outcomes (all compared between the baseline and week 12 or between the baseline and 1 year) of this study are (a change in):selected biomarkers: the interferon signature in peripheral blood cells, CXCL4, interleukin-1 beta (IL-1β), IL-6, tumor necrosis factor-alpha (TNF-α), ET-1, intercellular adhesion molecule 1 (ICAM-1) and vascular endothelial growth factor (VEGF) [3, 23–27];nailfold capillary changes other than capillary density and the presence of giant capillariesan mRSS; the presence of puffy fingers; the presence of synovitis; the presence of tendon friction rubs; fulfilling EULAR/ACR classification criteria for SSc [28];pulmonary function tests; the presence of interstitial lung disease; a suspicion of pulmonary hypertension; andphysical function, general health and utilities as measured by the Scleroderma Health Assessment Questionnaire (SHAQ), 36-Item Short Form Health Survey (SF-36), EuroQOL five dimensions questionnaire (EQ5D) and Gastrointestinal Tract Questionnaire (GIT).

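### The Discussion restricts entry to patients who do not meet the 2013 ACR/EULAR criteria, but the eligibility lists do not, so neither the stated population nor the classification outcome is secured as a measure of progression

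*Protocol article*

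**What the plan says.** Four sections of the protocol article bear on who is enrolled and how classification status is used.

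- **Discussion.** The first design issue it addresses is the choice of patients still in the inflammatory phase, and it gives the resolution as an entry rule: "the choice was made to include only patients who fulfil the VEDOSS criteria, but not the 2013 ACR/EULAR classification criteria, for SSc".
- **Inclusion criteria.** Besides adult age and Raynaud's phenomenon, the list asks for "positive test for anti-centromere or anti-topoisomerase antibodies AND nailfold capillaroscopic findings typical of SSc", and then "puffy fingers for less than 3 years, andmRSS of 0". ACR/EULAR status is not mentioned.
- **Exclusion criteria.** The list opens with "Patients who, at randomisation, meet any of the following criteria are not eligible for the study". It then names single features, such as "presence of acrosclerosis, acro-osteolysis or digital ulcers" and "clinically significant internal organ involvement: diffusing capacity for carbon monoxide (DLCO) less than 80% predicted", along with a further auto-antibody, earlier systemic treatment, other organ thresholds and contra-indications. Neither the classification set nor a score appears.
- **Secondary outcomes.** One item is "fulfilling EULAR/ACR classification criteria for SSc [28" (the quoted text breaks off inside the reference number). It cites the same source as the Discussion. The section presents its items as changes, compared between baseline and either week 12 or 1 year.

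The Study outcome rationale adds that nailfold capillary abnormalities form part of the ACR/EULAR classification criteria.

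**The concern.** The article gives two descriptions of its population. One requires that patients do not yet meet the 2013 classification. The other, which is the operative list, is silent on it. A site that applies the lists as printed would not have to check classification status.

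Two things depend on this. The first is the population to which the result applies: the Discussion justifies the restriction by the expected response of patients in the inflammatory phase, and it looks ahead to a phase III trial. The second is the reading of one secondary outcome. Fulfilling the classification marks progression only in a patient who did not fulfil it at the start. A patient who enters already classified and stays so would be counted as fulfilling it at follow-up without having progressed.

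**Working it through.** **Step 1: look for the restriction in the lists.**

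| Condition | Discussion | Inclusion criteria | Exclusion criteria |
|---|---|---|---|
| Meets VEDOSS | yes | yes | – |
| Does not meet 2013 ACR/EULAR | yes | absent | absent |
| Skin score of 0 | – | yes | – |
| No acrosclerosis, acro-osteolysis or digital ulcers | – | – | yes |
| No defined organ involvement | – | – | yes |

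The second row is the discrepancy.

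**Step 2: ask whether the other rows imply it.** The skin, digital and organ conditions remove single disease features and so make classification less likely. They would rule it out only if the features still permitted could never reach the cut-off. The article gives neither weights nor cut-off, so this cannot be shown. What it does show points the other way: a feature required of every patient, typical capillaroscopy, is itself an item of the ACR/EULAR set according to the Study outcome rationale. Every eligible patient therefore enters with at least one item present, and no listed step checks the total.

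**Step 3: illustrate the effect on the secondary outcome.** Let b be the share already fulfilling the criteria at randomisation. The article does not give b, so the values below are assumptions. The planned arms are 20 and 10 (Sample size). Patients able to newly fulfil the criteria number 20(1 − b) and 10(1 − b):

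| Assumed b | Methylprednisolone | Placebo |
|---|---|---|
| 0 | 20 | 10 |
| 0.25 | 15 | 7.5 |
| 0.50 | 10 | 5 |
| 1 | 0 | 0 |

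Suppose instead that all patients are analysed, that those already classified stay so, and that b is equal in both arms. If a proportion p of the others convert, the proportion fulfilling at follow-up is b + (1 − b)p. The difference between arms is then (1 − b) times the difference in conversion. At b = 0.50 it is halved.

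**Step 4: check that the primary design figure is untouched.** With SD 0.9, two-sided alpha 0.05 (two-sided is assumed), power 0.80 and 2:1 allocation, the placebo arm for a difference of 1.0 needs (1 + 1/2) × 0.9² × (1.960 + 0.842)² / 1.0² = 9.5, rounded up to 10. That gives 10 + 20 = 30, as stated. The detectable difference is 0.9 × (1.960 + 0.842) × √(1/10 + 1/20) = 0.98 by the normal approximation and 1.01 by the t distribution, which agrees with the article's figure of nearly 1.0. Classification status does not enter this calculation.

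**The case against.** The strongest defence is that the mismatch is one sentence in a Discussion. Entry is defined by VEDOSS, the broader conclusions speak of very early SSc, and patients admitted under the inclusion list meet that definition. The affected outcome is one item in a long secondary list of a 30-patient pilot. Randomisation means that baseline fulfilment does not by itself bias the comparison between arms. Much of this stands, and it limits the severity.

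Two stronger readings are tempting, and the article does not support them.

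- **That the population claim is false, because the entry features already add up to the classification.** This needs the weights and cut-off, which the article does not give. The listed exclusions also remove several features of more advanced disease. What can be said is that the claim is not secured.
- **That the classification outcome would be constant or void if everyone were already classified.** The Secondary outcomes section speaks of change and does not restrict it to new fulfilment. Change can go both ways: the Abstract hypothesises remission, and the presence of puffy fingers is itself followed. The 0 and 0 in the last row of the first illustration apply to new fulfilment only.

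Journal condensation is not a good answer. The article prints both lists in detail, down to numerical thresholds, and says that patients who meet the inclusion criteria are eligible.

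**Conclusion.** The inconsistency is real. The Discussion states an entry restriction that the eligibility lists do not contain, and the listed criteria do not secure it by implication. Patients who already fulfil the ACR/EULAR classification may be randomised, in the sense that nothing listed prevents it. For them, fulfilment at week 12 or 1 year does not indicate progression.

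The size is unknown: the share could lie anywhere from 0% to 100%, and the worked values of 25% and 50% are illustrations, not estimates. The halving at 50% also assumes no loss of fulfilment and equal shares in the two arms. The likely harm is a less precise or less interpretable result on one secondary outcome, and a population statement that may not match the patients enrolled. The primary endpoint and the sample size of 30 are unaffected. This is a consistency and interpretation point of moderate severity.

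**What to change.** 1. Reconcile the Inclusion criteria, Exclusion criteria, Secondary outcomes and Discussion, so that the population statement matches the patients who are actually eligible. If non-fulfilment of the 2013 criteria is intended, it belongs in the eligibility lists. If not, the Discussion sentence should be corrected. Because enrolment has begun, a new criterion would not change who has already been randomised, and it could slow recruitment.
2. Derive ACR/EULAR status at randomisation and report it by arm. The outcome is already to be compared with baseline, so the data should be at hand.
3. Define the progression outcome as new fulfilment, at week 12 or 1 year, among patients who did not fulfil the criteria at baseline. Report loss of fulfilment separately among those who did.
4. Settle this before the data are unblinded.

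The cost is wording, one derived baseline variable, and fewer patients contributing to this secondary outcome. Restricting the analysis is not free: at an assumed 50% already classified it would leave about 10 versus 5. The skin score and the lung outcomes already listed can still be analysed in all patients.

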### Trial status

Open for inclusion.

## Abbreviations

ACR: American College of Rheumatology
ASCT: Autologous haematopoietic stem cell transplantation
EULAR: European League Against Rheumatism
mRSS: Modified Rodnan skin score
NCM: Nailfold capillaromicroscopy
SSc: Systemic sclerosis
VEDOSS: Very early diagnosis of systemic sclerosis
